## Abstract

**Background:**

Anorexia nervosa (AN) and Obsessive Compulsive Disorder (OCD) are among the most incapacitating and costly of mental disorders. Cognitive Behaviour Therapy (CBT), medication, and combination regimens, to which in AN personalised guidance on weight control is added, are moderately successful, leaving room for more effective treatment algorithms. An underlying deficit which the two disorders share is cognitive inflexibility, a trait that is likely to impede treatment engagement and reduce patients’ ability to benefit from treatment. Cognitive remediation therapy (CRT) is an easy-to-use intervention aimed at reducing cognitive inflexibility and thereby enhancing treatment outcome, which we aim to test in a controled study.

**Methods:**

In a randomized-controlled multicenter clinical trial 64 adult patients with AN and 64 with OCD are randomized to 10 bi-weekly sessions with either CRT or a control condition, after which Treatment As Usual (TAU) is started. All patients are evaluated during single-blind assessments at baseline, post-CRT/control intervention, and after 6 months. Indices of treatment effect are disorder-specific symptom severity, quality of life, and cost-effectivity. Also, moderators and mediators of treatment effects will be studied.

**Discussion:**

To our knowledge, this is the first randomized controlled trial using an control condition evaluating the efficacy and effectiveness of CRT as a treatment enhancer preceding TAU for AN, and the first study to investigate CRT in OCD, moreover taking cost-effectiveness of CRT in AN and OCD into account.

**Trial registration:**

The Netherlands Trial Register NTR3865. Registered 20 february 2013.

## Background

Anorexia nervosa (AN) is a severely debilitating eating disorder characterized by self-starvation with both negative physiological and psychological effects. Individuals with AN assign extreme over-importance to body weight and shape, making it central to their self-evaluation, and develop an abnormal body-image perception.

Obsessive Compulsive Disorder (OCD) is characterized by recurrent obsessions and compulsions that cause marked distress and interfere with daily functioning [1]. More specifically, obsessions are defined as intrusive, repetitive thoughts, images, or impulses, and compulsions as purposeful, repetitive overt and covert behaviours performed to relieve obsessional distress.

Several studies have investigated potential relationships between AN and OCD based on the phenotypic features the two disorders have in common, such as repetitive and ritualistic behaviours, excessive habit formation, and cognitive rigidity [2]. Interestingly, several studies demonstrated rates of AN among OCD patients, and reversely rates of OC symptoms among AN patients to be higher than expected by chance, with OCD frequencies ranging between 9,5 and 62 % in patients with AN, and anorexia nervosa-rates up to 11–13 % in clinical OCD populations [3–8].

Further, there is accumulating evidence that patients suffering from AN and OCD share specific inefficiencies in executive functioning affecting attention processes, set-shifting/cognitive flexibility, processing speed, visuospatial abilities, inhibition of ongoing cognitive and motor responses, and working memory [9–14]. Specific inefficiencies in executive functioning are central to the development and maintenance of obsessions and compulsions as seen in both AN and OCD [15, 16].

It is suggested that particularly cognitive inflexibility maintains and exacerbates compulsive behaviours in both AN and OCD [17, 18]. Some degree of cognitive inflexibility is also found in first-degree relatives [19–21], i.e. a difficulty to shift to a different thought or action according to changes in a situation [22]. These inefficiencies are associated with the neurobiological (fronto-striatal) abnormalities associated with repetitive behaviours in AN and OCD [23]. Thus, patients seem to rely heavily on low-energy but highly automated and stereotyped repetitive behaviours, at the cost of higher-energy but more diverse goal-directed and flexible behaviours [24].

Furthermore, individuals with AN show a cognitive style in which there is a bias towards local or detailed-focus processing of information over the natural tendency to integrate information into a for the person relevant context [25]. In line with this, individuals with OCD show inefficiencies in global information processing and a detailed and less systematic organizational strategy [26, 27].

Finally and consistent with previous research, adults suffering from AN and OCD show specific visuospatial memory inefficiencies [26, 28, 29].

Arguably, these inefficiencies may prevent patients from successfully engaging in therapy and may decrease both treatment motivation and the efficacy of psychological interventions.

### Symptom-based treatment for OCD and AN

Treatment schemes for AN and OCD are generally aimed at symptom reduction. Standard treatment of adult AN consists of a combination of renourishment and psychotherapy. Clinical effects of either supportive clinical management, CBT, focal psychodynamic therapy, family therapy, or interpersonal psychotherapy are comparable [30–32]. Only 46% of patients recover fully, one third achieves partial improvement (showing residual symptoms), and 20% remains chronically ill [33]. One significant challenge in the treatment of individuals with AN concerns the ambivalence towards treatment. Intrinsic motivation to enable behavioural changes is often low [34].

According to European guidelines, the treatment of OCD should typically encompass CBT usually in combination with pharmacotherapy, specifically selective serotonin reuptake inhibitors (SSRIs) [35, 36]. Despite reasonable effect sizes (Cohen’s d around 1.0) [37–39], only 22% of OCD patients having received CBT recovers completely [37]. In a recent meta-analysis, Sharma et al. [40] found that 47% of all patients with OCD (treated or untreated) do not achieve complete remission. Thus, rates of incomplete recovery and treatment resistance remain relatively high [41, 42].

Moreover, in OCD non-compliance as to pharmacotherapy is common, as is dropout from CBT (with attrition rates between 13 and 27%) [43–47]. Dropout rates from treatment in outpatients with AN are even higher (ranging from 48 to 100%) [48].

Clearly, optimizing therapy results for AN and OCD remains a major challenge for both researchers and therapists. In the past decades various attempts have been made to develop supportive interventions to enhance adherence and effectivety, with an increasing interest in approaches that target underlying inefficiencies instead of the main symptoms of the disorder itself.

The relatively low success rates of guideline-directed therapies for AN and OCD, together with the inefficiencies in executive functioning that sufferers seem to share, have prompted the notion that patients might benefit from a training module that addresses and remediates these underlying inefficiencies.

### Cognitive remediation therapy

Recently, a cognitive intervention, i.e. Cognitive Remediation Therapy (CRT) has been adapted for eating disorders including AN, which specifically focuses on improving the cognitive inflexibility and organizational inefficiencies described above [49, 50]. CRT was originally developed for the treatment of patients with traumatic brain injuries but has also been applied in patients with attention deficit hyperactivity disorder (ADHD), learning disabilities [51] and schizophrenia. Although in schizophrenia results have been mixed, symptom reduction as well as improvement of cognitive and social functioning, and normalisation of neural activity have been described [52, 53]. CRT aims at improving cognitive flexibility, central coherence, global information processing, reducing perfectionism and improving the awareness of dysfunctional thinking styles.

In CRT for AN, patients carry out cognitive excercies and are encouraged to reflect on their typical, maladaptive daily-life strategies, and to consider and practice helpful alternatives, for instance by adopting more global ‘bigger-picture’ thinking strategies and more goal-directed behaviours. A recent meta-analysis on all available case reports has shown that CRT improves the cognitive performance of patients with severe AN and that the intervention is feasible and well tolerated [54]. Three recent randomized controlled trials (RCTs) similarly found evidence of its effectiveness in AN [55–57]. Dingemans et al. [57] demonstrated CRT preceding TAU to be more effective than TAU alone: the intervention boosted improvement in terms of ED-specific health-related quality of life (QoL) indices (Cohen’s d: 1.36), while ED-related psychopathology was lower at follow-up than it was following TAU alone (Cohen’s d: 0.99). Patients with relatively poor baseline set-shifting abilities showed greater long-term improvements in quality of life in the CRT group when compared to the control group. The authors accordingly concluded that CRT shows promise as a treatment enhancer. Although CRT has not directly been studied in OCD, two RCTs in OCD have tested similar approaches in OCD. Starting from the hypothesis of strengthening executive functions to foster later symptom reduction, Buhlman et al. [58] investigated a cognitive retraining program aimed at reducing organizational inefficiencies. Both OCD and control participants who underwent training improved more in organization and memory than participants who did not receive organizational training. The authors concluded that in OCD organizational capacities can be augmented. They however did not study the effects of this training on OCD symptoms. Second, in a promising RCT on the effects of a cognitive training program to improve organizational skills in 15 OCD patients compared to 15 controls, Park et al. [59] found that visual memory functions and obsessive-compulsive symptoms improved more in the treated group than in the control group.

## Methods/design

The study design is reported in line with the SPIRIT 2013 Statement (Standard protocol Items: Recommendations for Interventional Trials) [60]. The Medical Ethics Committee of the University Medical Centre Utrecht has approved the study (METc no. NL43751.041.13 v.03).

### Study aims

The primary goal of the current ongoing study is to examine the treatment enhancing effect of CRT on treatment as usual (TAU, guideline directed therapy) in AN and OCD. The secondary aim is to investigate the cost-effectiveness and budget impact of CRT. The third aim is to study which patient characteristics determine positive benefits from CRT-based treatment enhancement. More specifically, we study several moderators and mediators of response (Table 1).

**Table 1 Tab1:** Measures to assess screening, outcome, mediator and moderator variables

Function	Measure	Instrument	T0	T1	T2	T3
Screening	Diagnostic status	SCID	X			
Primary outcome	AN severity	EDE-Q	X	X	X	X
	OCD severity	Y-BOCS	X	X	X	X
Secondary outcome	OCD severity	OCI-R	X	X	X	X
	Quality of life	EQ-5D	X	X	X	X
		ED-Qol ^c^	X	X	X	X
		OCD-Qol ^b^	X	X	X	X
	Daily functioning	WSAS	X	X	X	X
	Healthcare utilization and production loss	TIC-P	X	X	X	X
	Depression	BDI-II	X	X	X	X
	General anxiety	BAI	X	X	X	X
Mediators	Cognitive flexibility	Stroop	X	X	X	X
		D-Flex	X	X	X	X
		TMT	X	X	X	X
	Response inhibition	SSRT	X	X	X	X
	Central coherence	GEFT	X	X	X	X
	Intolerance of uncertainty	IUS	X	X	X	X
	Perfectionism	CPQ	X	X	X	X
	Self-efficacy	PEPPI-5	X	X	X	X
	Behaviour inhibition/activation	BISBAS	X	X	X	X
	Therapeutic engagement	SRS ^a^	X			
Moderators	Demographics, e.g. sex, age, education level	Interview	X			
	Diagnostic status	SCID-I	X			
	Obsessive compulsive personality disorder	SCID-II-OCPD	X			
	Autism	AQ	X			
	ADHD	CAARS-S:SV ^b^	X			
	Cognitive flexibility	ID/EDS ^b^	X			
	Planning ability	BADS-Zoo-map	X			

*EDQ* Eating Disorder Examination Questionnaire, *Y-BOCS* Yale-Brown Obsessive Compulsive Scale, *OCI-R* Obsessive-Compulsive Inventory-revised, *EQ-5D* EuroQuol, *ED-Qol* Eating Disorder Quality of life questionnaire, *OCD-Qol* Obsessive-Compulsive Disorder Quality of life questionnaire, *WSAS* Work and Social Adjustment Scale, *TIC-P* Trimbos/iMTA Questionnaire for Cost Associated with Psychiatric Illness, *BDI-II* Beck Depression Inventory, second revision, *BAI Beck* Anxiety Inventory, Stroop Stroop task, *D-FLEX* Detail and Flexibility Questionnaire, *TMT* Trail making test, *SSRT* Stop Signal Reaction Task, *GEFT* Group embedded figures Test, *IUS* Intolerance of uncertainty scale, *CPQ* Clinical perfectionism questionnaire, *PEPPI-5* Perceived Efficacy in Patient-Physician Interactions, *BISBAS* Behavioural Inhibition and Behavioural Activation Scales, *SRS* Session Rating Scale, *SCID-I* Structured Clinical Interview for DSM-IV-TR Axis I disorders, *SCID-II* Structured Clinical Interview for DSM-IV-TR Axis II disorders, section obsessive-compulsive personality disorder, *AQ* Autism-spectrum Quotient, *CAARS-S:SV* Connors’ Adult ADHD Rating Scales, self report, short version, *ID/EDS* Intra dimensional-/extra dimensional shift paradigm, *BADS-Zoo* map Behavioural Assessment of the Dysexecutive Syndrome, Zoo Map

^a^ after each CRT/SAT session

^b^ OCD Only

^c^ AN Only

Our research questions read as follows:To what extend does CRT prior to TAU for AN and CBT for OCD enhance treatment outcome?To what extend is addition of CRT to TAU more cost-effective?What are moderators of treatment-enhancing effect of CRT in AN and OCD?What are mediators of treatment-enhancing effect of CRT in AN and OCD?

### Design

Figure 1 provides an overview of the study design. In a randomized controlled multicentre trial, we compare two treatment arms, i.e. CRT and, in the control condition, Specialized Attention Therapy (SAT), both delivered in 10 twice weekly sessions as an adjunct to TAU for AN and OCD. Patients are assessed at baseline (T0), directly following CRT or SAT completion and prior to symptom based TAU (T1), at 6 months after T0; (T2), and at 12 months after T0 (T3). All patients receive both oral and written information and are enrolled after they have provided written informed consent.

**Fig. 1 Fig1:**
[figure not shown]
Study design

### Participants

Patients aged between 18 and 60 years are recruited from four Dutch tertiary clinics specialized in the treatment of anxiety and eating disorders. Patients diagnosed with AN (both restrictive and binge/purge subtype) are recruited from Altrecht Eating Disorders Rintveld, Zeist, and Rivierduinen Eating Disorders Ursula, Leiden, and patients with OCD from Altrecht Academic Anxiety Centre, Utrecht, and Overwaal Centre for Anxiety Disorders, Nijmegen. Most of the patients referred to these centres suffer from moderate to severe AN or OCD.

Eligible are patients whose AN (or eating disorder not otherwise specified, clinically referred to as AN) or OCD diagnosis is consistent with the Diagnostic and Statistical Manual of Mental Disorders, fourth edition text revision (DSM-IV-TR ).

The criteria for exclusion are: severe neurological illness (including a history of seizures, stroke, or Parkinson’s disease), severe comorbid psychiatric disorder (clinical significant major depressive disorder, current acute phase of bipolar disorder, current psychosis, substance dependence/abuse), intellectual impairment, defined as an IQ < 80, estimated with the Dutch Adult Reading Test (DART) [61], which is a Dutch version of the National Adult Reading Test (NART) [62], and inability to adequately speak or read Dutch. Current use of antidepressants and antipsychotics is allowed provided that dosages are kept constant during the experimental part of the study. Since benzodiazepines can dampen the effect of cognitive treatments [63], their use is restricted to a daily maximum dose (up to 20 mg for temazepam or an equivalent dose) taken as a sleep medication. On request, patients can withdraw their participation at any time.

Inclusion and exclusion criteria are verified with the aid of the structured clinical interview for DSM-IV-TR axis I disorders (SCID-I [64]), while for OCD patients to be enrolled, a Yale-Brown Obsessive-Compulsive Severity Scale score ≥16 is required [65, 66]. In all patients comorbidity with either OCD or AN is allowed.

### Procedure and randomization

All participating centres adhere to standardized intake and screening procedures. The therapist performing the screening informs patients meeting the inclusion criteria about the study and ask their permission to have a research assistant contact them by phone or in person to invite them to participate in the trial, after which interested patients are sent or given a brochure describing the study. At least 1 week later baseline assessments are carried out after written informed consent is obtained. After baseline assessments patients not meeting inclusion-criteria are excluded. Patients satisfying all the study criteria are subsequently randomized to one of the two study conditions. An independent research coordinator who is not involved in the therapies or assessments uses SPSS/IBM [67] to create a randomization sequence stratified by treatment centre with a 1:1 allocation using random block sizes of 4. Given the nature of the study design, all patients and therapists are aware of the treatment condition (CRT or SAT). Patients are informed that both treatment arms are being investigated as to their potential to enhance subsequent TAU. The therapists delivering CRT or SAT are instructed not to reveal the treatment condition to the research assistant conducting the assessments; unintended violation of assessor blindness is recorded.

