### Specialized Attention Therapy (SAT)

SAT has been designed as the control intervention specifically for this trial. SAT is delivered by the same health professionals delivering CRT. The SAT session structure (10 twice weekly, 45-min sessions and homework assignment) is the same as in CRT. However, during SAT, cognitive flexibility, central coherence, global information processing skills, awareness of thinking styles, and reducing perfectionism are not addressed. Instead, after each task patients are asked their opinion on whether they (dis)liked the task. As a treatment rationale, patients are explained that SAT aims at helping them to focus on positive experiences by means of tasks and exercises, where each session–again in line with CRT–comprises different exercises. For an overview of the exercises practiced in SAT, see Table 3; for a more detailed description of the exercises, the SAT treatment manual is available upon request [120].

**Table 3 Tab3:** SAT exercises

Motor tasks	Djenga Mikado Leaning Tower of Pisa Operation Game
Luck tasks	Game of the Goose Ludo Snakes and ladders
Collaboration task	Drawing a picture together
Picture tasks	Spot the differences Viewing a picture
Verbal tasks	Last letter-first letter Incomplete sentences task Poems
Additional tasks	Listening to music Analogies Categories

From session 2 onward, patients are encouraged to engage in similar activities at home that they enjoy.

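### The stated block size is a single fixed 4 within each centre, so allocations are partly foreseeable to anyone who has followed them: an avoidable risk of selection bias, not a demonstrated one

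*Protocol article*

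**What the plan says.** In the section Procedure and randomization, the coordinator is to "create a randomization sequence stratified by treatment centre with a 1:1 allocation", and the sentence ends "using random block sizes of 4". No second block size is given anywhere. Under Participants, patients are "recruited from four Dutch tertiary clinics specialized in the treatment of anxiety and eating disorders", so there are four strata.

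The same randomization section separates list generation from the sites: "An independent research coordinator who is not involved in the therapies or assessments uses SPSS/IBM". It also says that patients and therapists know which intervention is given, that a therapist does the screening, and that the research assistant who carries out the assessments is to be kept blind, with accidental breaches recorded. Between baseline and randomisation there is a further eligibility step: "After baseline assessments patients not meeting inclusion-criteria are excluded".

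Under Specialized Attention Therapy (SAT), "SAT is delivered by the same health professionals delivering CRT". Under Study aims, the article describes the study as still ongoing.

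**The concern.** A block size can be random only if it can take more than one value. With one value, the sentence either describes a fixed block of 4, with only the order inside the block being random, or it misreports a scheme in which the sizes did vary. It needs correcting on either reading.

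On the first reading there is a design weakness. With a fixed, known block size, past allocations reveal future ones. An independent coordinator keeps the list out of sight, but cannot prevent deduction from allocations that are already open. Here they are open to therapists, and the team delivering one arm also delivers the other. If somebody with influence over who is referred, when a patient is booked, or who is judged ineligible after baseline could foresee the next arm, patients could be steered and the arms would no longer be comparable by design.

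A second consequence concerns blinding. An assessor who learns the arms of some patients in a block may be able to deduce the others. Among the primary outcomes this matters mainly for the Y-BOCS, which is clinician-rated. The EDE-Q is self-reported.

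**Working it through.** **Inputs.** Block size 4, ratio 1:1, stratification by centre (Procedure and randomization). Four centres (Participants). Total 128 patients (Power and sample-size calculation). The article gives no predictability figure of its own to reproduce.

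**Certain allocations, block of 4.** There are 4!/(2!·2!) = 6 equally likely orders: AABB, BBAA, ABAB, ABBA, BABA, BAAB. An allocation is certain once one arm has been used up.
- AABB and BBAA: positions 3 and 4 are certain, 2 each.
- The other four orders: only position 4 is certain, 1 each.
- Expected number per block = (2×2 + 4×1)/6 = 8/6 = 4/3.
- Share = (4/3)/4 = 8/24 = 33.3%.

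This is an average. A single block has at least one certain allocation (25%) and at most two (50%). Over 128 patients in complete blocks it amounts to 128/3 ≈ 43 allocations.

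**Best guess, block of 4.** The observer always names the arm with more places left and tosses a coin if they are equal.
- Position 1: 1/2.
- Position 2: 2/3.
- Position 3: first two alike (probability 1/3), certain; otherwise a coin toss. 1/3×1 + 2/3×1/2 = 2/3.
- Position 4: 1.
- Mean = (1/2 + 2/3 + 2/3 + 1)/4 = 17/24 = 70.8%.

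Simulation of the same scheme gave 33.3% and 70.8%.

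**What a breach of assessor blinding reveals.** Three known allocations in a block always give the fourth. Two known allocations settle the rest only if they are in the same arm. Of the 6 pairs in a block, 2 are same-arm pairs, so the chance is 1/3. With one patient known in each arm, nothing further is certain.

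**Varying sizes.** These figures are simulated, assuming 32 patients per centre (128/4, that is, even recruitment, which the article does not state), sizes drawn with equal probability, and an observer who sees every earlier allocation and knows the set of sizes but not their order.

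| Block sizes | Certain in advance | Best guess correct |
|---|---|---|
| 4 only | 33.3% | 70.8% |
| 4, 6 | 5.7% | 68.8% |
| 2, 4, 6 | 4.0% | 69.8% |
| 4, 6, 8 | 2.3% | 67.5% |

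A second simulation of 3,000 centres gave 2.4% and 67.6% for sizes 4, 6 and 8. Varying the sizes therefore removes nearly all certainty but lowers the best guess by only about 3 percentage points.

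**The case against.** The strongest reply is that the arithmetic describes an observer whom the article never shows to exist. A reader might infer that the therapists see every earlier allocation at their centre and that the screening therapist is one of them. The text does not support this. It says that therapists know the treatment condition, not that any one of them follows all allocations in order or knows where blocks begin. It refers separately to the therapist who screens and to the therapists who deliver the interventions, and does not say whether they are the same people. This part of the objection stands.

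The route to steering is also longer than it first appears. The screening therapist informs patients and asks permission for contact, a research assistant then invites them, baseline follows at least a week later, and randomisation comes after that. Which slot a patient will fill is hard to foresee at screening. A reader might also infer that exclusions after baseline are decided by someone who knows the next arm. The article does not say who decides, and eligibility is checked with a structured interview and, for OCD, a score threshold. Nor does it say that breaches of assessor blinding are expected, only that they are recorded.

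Finally, the word random may refer to the order within blocks, and how allocations are released may be set out in a full protocol that is not shown. The first would be a slip of language that still leaves a fixed size of 4. The second is fair, and no missing release procedure is alleged here. Neither changes the fact that one size is stated, and stated publicly.

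**Conclusion.** The point holds as a wording error joined to an avoidable design risk. As written, the scheme is a fixed block of 4 per centre. For an observer who knows the size and has followed the centre's earlier allocations, one third of allocations are certain on average and 71% can be guessed. Both figures are exact for complete blocks. Open allocation among therapists and shared delivery staff make such knowledge plausible, but the article does not document it.

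The stronger conclusion, that recruitment or assessment has been biased, is not supported. Any effect on the outcome comparison cannot be sized from the article. The planned sample size, alpha and power are unaffected. The change is worth making because it is cheap, but it does not make the allocation unpredictable.

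**What to change.** 1. **If patients remain to be randomised:** the independent coordinator generates a new list for each centre, with block sizes drawn at random from, for example, 4, 6 and 8, and does not disclose the sizes to site staff or assessors.
2. **In all cases:** replace the phrase with a statement of what was done, either fixed blocks of 4 or randomly varying sizes. If the sizes in fact varied, say so without listing them while recruitment is open. The article calls the study ongoing but does not give recruitment status. If recruitment has closed, this correction is all that remains.

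**Cost:** new computer-generated lists and one sentence. The largest imbalance within a centre from an incomplete block rises from 2 (half of 4) to 4 (half of 8). A block left unfinished when the lists are switched can add up to 2 more, so at most 6 in a centre.
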